#### Intervention

The intervention clusters receive a multifaceted ASI. The control clusters provide care as usual. The intervention period was intended to last 4 months. After a month, it was interrupted by the first wave of the COVID-19 pandemic, resulting in a 6-month pause. On restart in September 2020, the pragmatic choice was made to restart the intervention period with a duration of 2–3 months, depending on the local situation.

##### Decision tool and toolbox

At the core of the ASI is a decision tool to guide the use of antibiotics for suspected UTIs in frail elderly (online supplemental data 2).^1^ It promotes an active monitoring approach in case only non-specific symptoms are present. This decision tool is incorporated in the Dutch UTI guideline for elderly care medicine and congruent with the Swedish and Norwegian UTI guidelines.^20–22^ To support the implementation of the decision tool, a toolbox of educational materials is composed (figure 2 and online supplemental data 3). First, a generic toolbox is designed, centred around the decision tool. Next, it is tailored to become country-specific by the local researchers, based on the qualitative study data and any locally available materials. During the intervention period, further tailoring may take place within the participating cluster itself (figure 2).

**Figure 2 F2:**
[figure not shown]
Toolbox. The educational materials and targeted stakeholders in the generic toolbox are listed, and the tailoring process is shown. GP, general practitioner.

##### Implementation: modified PAR approach

The intervention is tailored based on an analysis of the interview data to identify country-specific barriers and facilitators. For example, the roles of the healthcare professionals and knowledge gaps in care for UTIs differ per country and need to be targeted accordingly. During the intervention period, the researchers and healthcare professionals together go through a cyclical process of reflection, planning and action during sessions for education and evaluation. These sessions combine a top-down and bottom-up approach; both education on the decision tool and any knowledge gaps identified in the qualitative study, as well as reflection and planning for local implementation. The aim is to go through at least two PAR cycles in each cluster, and to actively involve physicians as well as nursing staff. Further tailoring may be performed in each country and cluster locally.

#### Outcome assessments

##### Primary outcome measure

Number of prescriptions of antibiotics for suspected UTIs.

##### Secondary outcome measures

Number of prescriptions of antibiotics for suspected UTIs in office hours.Number of incorrect prescriptions of antibiotics for suspected UTIs.Incidence of suspected UTIs.Incidence of complications within 21 days after each UTI suspicion (presence yes/no of a complication: delirium, pyelonephritis, sepsis and renal failure).Incidence of referral to a hospital within 21 days after each UTI suspicion.Incidence of hospital admission within 21 days after each UTI suspicion.Mortality.Mortality within 21 days after each UTI suspicion.All outcomes are assessed during the follow-up period, and expressed per patient-year.

#### Data collection

Data are collected during a 5-month baseline period and a 7-month follow-up period, through case report forms (CRFs) completed by the GP, nurse or researcher based on contact with a healthcare professional or medical file. The timeline for participating clusters and participants is displayed in figure 3.

**Figure 3 F3:**
[figure not shown]
Timeline of the cluster randomised controlled trial. The periods of data collection and procedures are shown for the clusters and participating patients. CRF, case report form; UTI, urinary tract infection.

For each participant, a CRF with patient characteristics is filled in at study entry consisting of items concerning demographics, ADL dependency measured through the Katz Index of Independence in Activities of Daily Living,^23^ and relevant medical history. The GPs prospectively register each UTI suspicion on a short registration form, describing symptoms, diagnostics, and antibiotic treatment (primary and secondary outcomes). After 7 and 21 days, follow-up forms are filled in to assess the course of disease, any change in antibiotic treatment, complications, and mortality (primary and secondary outcomes). Overall mortality (secondary outcome) is registered on exclusion of a patient. Any missing data are retrospectively registered through consultation of GPs, nurses and/or access of the medical records.

Furthermore, anonymised data concerning COVID-19 incidence in the participating care organisations are registered during the follow-up period.

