#### Eligibility criteria and recruitment

Recruitment of clusters is performed through the networks of the research groups in Poland, the Netherlands, Norway and Sweden. The care organisations identify eligible patients, provide written study information, and ask whether they may be approached by the research team. Written informed consent from patients (or representatives in case of legal incapacity) is obtained by a visiting researcher or nurse.

For inclusion, patients need to be 70 years or older, have physical and/or mental disabilities and ADL dependency requiring care, do not use prophylactic antibiotics, do not receive hospice care and are estimated not to have a very limited life expectancy (≤1 month). Patients are excluded when they start prophylactic antibiotics, start receiving hospice care, have a limited life expectancy (≤1 month), pass away, or move away from the cluster. Patients need to be included for at least 2 months to contribute data to the study.

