## Ethics and dissemination

### Participant safety and monitoring

The cluster RCT is considered low risk, as the intervention corresponds to current guidelines. There is no data monitoring committee, and any SAEs are not reported. No interim analyses are planned. For both the qualitative study and cluster RCT respectively, ethical approval was given by the Committee of Bioethics of the Medical University of Lodz, Poland (RNN/381/18/KE and RNN/260/19/KE), the Regional Committee for Medical and Health Research Ethics in Norway (2018/2191/REK sør-øst A and 2018/2521/REK sør-øst A), and the Swedish Ethical Review Authority (2019-00504 and 2019-00796/1228-18 (2019-02541)). In the Netherlands, the Medical Ethics Review Committees established that approval was not required since the Medical Research Involving Human Subjects Act does not apply (2018.500 VU University Medical Centre and WAG/mb/19/012207 University Medical Centre Utrecht). Substantial protocol modifications are communicated to ethical committees and the trial register. Dissemination will take place through publication and presentations. Furthermore, an implementation package will be developed.

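### Deaths after exclusion for hospice care or a life expectancy of 1 month or less are not captured by the stated procedure for overall mortality

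*Protocol article*

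**What the plan says.** Two sections of the protocol article have to be read together.

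- **Eligibility criteria and recruitment** sets out when a resident leaves the study: "Patients are excluded when they start prophylactic antibiotics, start receiving hospice care, have a limited life expectancy (≤1 month), pass away, or move away". Hospice care and short prognosis are triggers in their own right, distinct from death.
- **Data collection** (text after Figure 3) fixes when overall mortality is recorded: "Overall mortality (secondary outcome) is registered on exclusion of a patient". No check of vital status after exclusion is described.

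Secondary outcome measures lists overall mortality and, separately, "Mortality within 21 days after each UTI suspicion". The second outcome has its own capture: "After 7 and 21 days, follow-up forms are filled in to assess the course of disease, any change in antibiotic treatment, complications, and mortality". Data collection then adds: "Any missing data are retrospectively registered through consultation of GPs, nurses and/or access of the medical records".

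On oversight, Participant safety and monitoring states: "There is no data monitoring committee, and any SAEs are not reported". Randomisation and blinding says that blinding is not possible. Data analysis adopts the intention-to-treat principle.

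**The concern.** A resident recognised as dying leaves the study at that moment, and overall mortality is registered at that moment. The exclusion record is then complete, with the resident alive, and the expected death falls outside the stated capture. Follow-up stops because death is near, so the censoring is informative. Expressing the outcome per patient-year does not repair this: a short-prognosis exclusion removes roughly a month of person-time but the whole event.

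The intervention promotes restrictive antibiotic use, so mortality bears directly on its safety. With no data monitoring committee and no SAE reporting, the article describes no other route that would recover deaths after exclusion. Recognition of a terminal phase is a judgement made by staff who know their cluster's allocation, so the loss need not be equal between arms. Stopping outcome capture on an event after randomisation also sits badly with intention to treat.

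**Working it through.** **The plan's own figures.** The article states no mortality figure to reproduce. Its sample size concerns the primary outcome only. A tie-corrected Wilcoxon calculation (Poisson means 0.75 × 7/12 = 0.4375 and 0.4 × 7/12 = 0.2333, one-sided alpha 0.05, power 0.8) gives 216.8 patients. Multiplied by the design effect 1 + 9 × 0.06 = 1.54, this is 333.8, against 333 stated. Nothing below depends on it.

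**Step 1: which deaths are captured.**

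| Path | Status when mortality is registered | Captured as overall mortality? |
|---|---|---|
| Death with no earlier exclusion | Dead (death is itself an exclusion reason) | Yes |
| Exclusion for hospice care, then death | Alive | Not by the stated procedure |
| Exclusion for life expectancy of 1 month or less, then death | Alive | Not by the stated procedure |
| Death within 21 days of a suspicion, after exclusion | Alive | For the 21-day outcome: depends on whether the day 7 and day 21 forms continue, which is not stated |

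**Step 2: how many deaths could be missed.**

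- From the article: 680 residents, 7 months of follow-up.
- Assumed, because the article gives neither: annual mortality *m* of 15-35%, and share *f* of deaths preceded by a hospice or prognosis exclusion of 10-75%. The hazard is taken as constant.
- Deaths in follow-up = 680 × [1 − (1 − *m*)^(7/12)]. Uncaptured deaths = *f* × that number.

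| Annual mortality | Deaths in 7 months | *f* = 10% | *f* = 25% | *f* = 50% | *f* = 75% |
|---|---|---|---|---|---|
| 15% | 61.5 | 6.2 | 15.4 | 30.8 | 46.1 |
| 25% | 105.1 | 10.5 | 26.3 | 52.5 | 78.8 |
| 35% | 151.1 | 15.1 | 37.8 | 75.5 | 113.3 |

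The span is about 6 to 113. It treats all 680 recruits as at risk for 7 months. Sample size plans on 10 of the 20 recruits per cluster each contributing 7 months. With 34 × 10 = 340 residents the counts halve, to about 3 to 57.

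**Step 3: effect on the comparison.** Little person-time is removed, so the observed rate ratio is about the true ratio × (1 − *f* in intervention) / (1 − *f* in control). The shares below are illustrative.

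| True ratio | *f* intervention | *f* control | Observed ratio |
|---|---|---|---|
| 1.0 | 50% | 50% | 1.00 |
| 1.3 | 50% | 50% | 1.30 |
| 1.0 | 60% | 40% | 0.40/0.60 = 0.67 |
| 1.0 | 40% | 60% | 0.60/0.40 = 1.50 |
| 1.3 | 60% | 40% | 1.3 × 0.40/0.60 = 0.87 |

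Equal loss lowers the death rate in both arms and leaves the ratio about where it was. Unequal loss moves it in either direction.

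**Adjacent point, not counted above.** The eligibility section also says: "Patients need to be included for at least 2 months to contribute data to the study". The text does not say whether this rule applies to mortality.

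**The case against.** The article condenses a fuller protocol, and the content of the exclusion form may be specified there. Retrospective completion from GPs, nurses and records could be used to find later deaths. Mortality is one of eight secondary outcomes, complications, referral and admission are also collected, and the intervention is described as low risk and in line with guidelines. These arguments lower the severity. They do not remove the point, because the article does state when overall mortality is registered, and that time combines badly with its own exclusion triggers. A death after exclusion is not a missing value on a completed record, and nothing extends the completion clause beyond exclusion.

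Three stronger readings are tempting, and the article does not support them:

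- A reader might infer that all mortality is recorded only at exclusion. The 21-day outcome has its own forms. Whether they continue after exclusion is unclear, so those deaths cannot be called lost.
- A reader might infer that many deaths, or most, disappear. The article gives no figure from which to say so, and deaths without an earlier hospice or prognosis exclusion are counted.
- A reader might infer that the treatment comparison is biased. That requires such exclusions to differ between arms, for which the article offers no evidence. It is a risk, not a demonstrated error.

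**Conclusion.** The point holds for overall mortality as a defect in data capture: the stated time of registration precedes deaths that follow a hospice or short-prognosis exclusion. Its size cannot be derived from the article. The range of about 6 to 113 among 680 rests entirely on the assumed mortality and share, on a constant hazard, and on no later capture. The absolute death rate is understated to that extent. Distortion of the rate ratio depends on unequal loss between the unblinded arms. For 21-day mortality the finding is an ambiguity to resolve. The primary outcome and the sample size are untouched, so this is a cheap improvement to a safety-relevant secondary outcome and does not threaten the main result.

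**What to change.** 1. For every enrolled resident, record vital status and date of death to the end of the 7-month follow-up, whatever the reason for exclusion, from the care organisation or the medical records that the trial already consults. Count person-time for mortality to death or the end of follow-up, separately from person-time for prescriptions.
2. State that a 21-day form open at exclusion is still completed.
3. Report exclusions by reason and arm, so that readers can see whether hospice and prognosis exclusions are balanced.

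The cost is one extra data item per excluded resident and a short amendment, with a check that existing consent covers it. Trial status places database lock in September 2021, after the expected end of the trial in July 2021, so the item could be collected retrospectively before lock. The change concerns data capture and reporting only. Clinical management and the primary outcome stay as they are.

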#### Data management

Data are collected pseudonymised on paper forms, using a study code for each patient. Afterwards, they are electronically registered in the secured online database Research Online, according to regulations of the International Conference on Harmonisation - Good Clinical Practice. Research Online has multiple validation rules built into the eCRFs. The data cleaning process is supported by automatically and manually generated queries. At the end of the study, all data will be locked. Dedicated data sets are provided to the researchers for analysis. Data are kept securely for at least 15 years.

#### Data analysis

The analysis will follow the intention-to-treat principle. For the primary outcome, a generalised linear mixed model for Poisson distributions will be used. In case the assumptions for Poisson distributions are insufficiently met, other distributions will be considered (ie, negative binomial, generalised Poisson, zero-inflated Poisson). A random intercept will be included to correct for clustering within care facility and/or GP, and an additional random intercept will be included to correct for repeated measurements in patients. When results indicate no or very low clustering at the facility/GP or patient level, the corresponding random intercept will be excluded from the analysis. The comparison between intervention and control group, estimated with the time by treatment interaction, will be reported as Rate Ratio’s with a 95% CI and a corresponding p value. In a second model, prespecified prognostic factors will be added: age, gender, ADL dependency, presence of an indwelling catheter, dementia, recurrent UTIs, diabetes mellitus, and kidney disorders. In case there are missing values on baseline variables that were selected as potential confounders, multiple imputation will be considered. Furthermore, subgroup analysis will be performed to assess outcomes in groups per country, with different gender, age, presence of dementia, urinary incontinence and indwelling catheter.

#### Process evaluation

A process evaluation is conducted in the care organisations participating in the cluster RCT. The framework described by Saunders *et al*
24 is used. Elements that are assessed include fidelity, dose delivered/received, reach, recruitment and context (including COVID-19 impact). Data are collected through documentation of the intervention process by the researchers, and through questionnaires with closed-ended and open-ended questions to participating healthcare personnel. Quantitative data will be reported using descriptive statistics; thematic analysis will be performed on the qualitative data.

### Patient and public involvement

In the qualitative study, patients and informal caregivers are interviewed. These data were taken into account in the intervention implementation in the cluster RCT. In the process of the design of the cluster RCT, a meeting was held with representatives of Network Utrecht, care for the elderly (NUZO), Julius Centre, University Medical Centre Utrecht, The Netherlands. Their suggestions on the protocol were taken into account; for example, on patient-directed toolbox materials.

## Discussion

We perform a European qualitative study exploring factors influencing decision making on UTIs in frail elderly, and a pragmatic cluster RCT to assess the effect of a decision tool to improve antibiotic prescribing for UTIs in frail elderly, implemented using a PAR approach. We believe this combination of methodologies is essential to address the complexity of decision-making on UTIs in this population. Drawing lessons from the Improving Rational Prescribing of Antibiotics in Long-term Care Facilities (IMPACT) study,^25^ we are the first to apply this in a diverse international setting.

The PAR approach for implementation allows us to embrace the heterogeneity of the elderly care settings within and between countries.^26^ With large-scale nursing homes in some countries and small-scale living facilities in others, an identical ASI for each healthcare professional will not be effective. Tailoring the intervention using PAR promotes bottom-up engagement of healthcare professionals, thereby enabling the required behavioural changes for lasting effects.

Inherent to the tailored approach are limits in the ability to exactly replicate our results. Nevertheless, the methods are replicable, and we believe our results will be widely applicable. The qualitative study will offer in-depth understanding of the factors involved in decisions on UTI, thereby creating opportunities for future ASI development. Our robust trial design, in line with epidemiological recommendations for evaluating ASI,^27^ will provide evidence on the application of the latest UTI guidelines. Furthermore, our process evaluation will generate understanding on the ASI and its components in the various settings, and will provide lessons on the use of PAR in future trials. A practical implementation package will become available, with relevant toolbox materials and lessons for daily practice to be tailored to any setting. A further limitation of our study is that we cannot collect data on overall antibiotic use, as we focus on prospective registration in included patients of suspected UTIs only.

The cluster RCT was interrupted by the first wave of the COVID-19 pandemic during the intervention period, and was forced to pause for 6 months. Restarting required much flexibility from the participating care organisations, where patient care already suffered from the pandemic. Sessions for the intervention meeting had to be repeated (mostly online). Furthermore, the 6-month delay and further COVID-19 waves regrettably continue to lead to the passing away of participants, increasing the need for new recruitment. As randomisation takes place per country, we presume effects of COVID-19 on our population characteristics and outcomes, if any, will be balanced between intervention and control clusters.

In conclusion, we aim to evaluate the effectiveness of a multifaceted ASI to reduce antibiotic prescribing for UTIs in frail elderly through a qualitative study and cluster RCT in Poland, the Netherlands, Norway and Sweden. Our tailored approach within the diverse setting is promising to yield broadly applicable results, even if currently challenged by the COVID-19 pandemic.

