#### Design and setting

A cluster RCT is performed in nursing homes in Poland, the Netherlands, Norway and Sweden, and in residential care homes and home care organisations in the Netherlands, attended by GPs. More details on the setting are provided in the online supplemental data 1. The cluster and unit of randomisation is the care organisation linked to the GP practice; one care organisation may be attended by multiple GP practices or vice versa. In the final months of the study period, a process evaluation is performed.

10.1136/bmjopen-2021-052552.supp1Supplementary data

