#### Randomisation and blinding

Clusters are randomised to intervention or usual care, using SAS software V.9.4 by an independent data manager.^19^ Block randomisation is used to assign clusters to intervention or control in each country, stratified on cluster size (small/medium/large). Due to the nature of the intervention, blinding is not possible; however, the aims of the study outcomes are not explicitly stated to the control clusters to avoid contamination.

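### Residents recruited after the intervention started are not covered by the presumed balance from randomisation, and the first model does not adjust for who they are

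*Protocol article*

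**What the plan says.** All references are to the protocol article.

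- **Unit and blinding.** Design and setting: "The cluster and unit of randomisation is the care organisation linked to the GP practice". Randomisation and blinding: "Due to the nature of the intervention, blinding is not possible". The same section adds that control clusters are not told the aims explicitly.
- **Who finds residents.** Eligibility criteria and recruitment: "The care organisations identify eligible patients, provide written study information, and ask whether they may be approached by the research team". Written consent "is obtained by a visiting researcher or nurse". Two months of inclusion is enough to contribute data.
- **Timing.** Intervention, on the intervention period: "After a month, it was interrupted by the first wave of the COVID-19 pandemic, resulting in a 6-month pause". Discussion: "The cluster RCT was interrupted by the first wave of the COVID-19 pandemic during the intervention period". The Discussion then says that the delay and "further COVID-19 waves regrettably continue to lead to the passing away of participants, increasing the need for new recruitment".
- **Reassurance.** The same paragraph of the Discussion presumes that any COVID-19 effects on population characteristics and outcomes are balanced between arms, because randomisation is done within country.
- **Analysis.** Data analysis specifies a Poisson mixed model with random intercepts for facility and/or GP and for patient, with the treatment effect taken from the time-by-treatment interaction. Eight resident factors (age, gender, ADL dependency, indwelling catheter, dementia, recurrent UTIs, diabetes, kidney disorders) enter only in a second model.

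**The concern.** Cluster randomisation protects the comparison of clusters, and of residents whose inclusion could not depend on the arm. It does not protect the comparison of residents who enter once the arm is known to those who identify them. Randomising within country can spread COVID-19 exposure evenly over the arms. It cannot make the residents put forward afterwards alike.

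The baseline period does not rescue the contrast. It comes before the intervention period, so anyone recruited after the intervention start has follow-up data only. If such recruits differ in UTI risk between arms, the resident mix changes from baseline to follow-up in one arm and not in the other, and the interaction reads that change as a treatment effect. At stake is the validity of the primary rate ratio. Its precision is not the issue.

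**Working it through.** **Inputs from the article.** Assumed rates are 0.75 and 0.40 prescriptions per person-year (Sample size), so the planned rate ratio is 0.40/0.75 = 0.533. Data collection covers 5 months at baseline and 7 months at follow-up. The article gives no number, share or entry dates for new recruits, so it has no figure of its own on this point to reproduce. The sample size of 333 is not in dispute: a tie-corrected Wilcoxon calculation with design effect 1 + 9 × 0.06 = 1.54 gives 216.8 × 1.54 = 333.8.

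**Assumed inputs.** Let f be the share of intervention-arm follow-up person-time contributed by residents recruited after the intervention start, taken as 0.20 to 0.50. Let k be their underlying risk relative to other residents, taken as 0.80 or 1.20. Control-arm recruits are taken as unselected.

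**Effect on the contrast.** In crude form, the interaction is

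(intervention follow-up rate / intervention baseline rate) ÷ (control follow-up rate / control baseline rate).

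Late recruits contribute to neither baseline rate. Only the intervention follow-up rate changes, by the factor

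m = (1 − f) + f × k,

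so the crude rate ratio becomes the true rate ratio × m.

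| f | k | m (true ratio 1.00) | true ratio 0.533 becomes |
|---|---|---|---|
| 0.20 | 0.80 | 0.80 + 0.16 = 0.96 | 0.512 |
| 0.50 | 0.80 | 0.50 + 0.40 = 0.90 | 0.480 |
| 0.20 | 1.20 | 0.80 + 0.24 = 1.04 | 0.555 |
| 0.50 | 1.20 | 0.50 + 0.60 = 1.10 | 0.587 |

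The crude shift is therefore 4-10% either way. It scales with the assumed risk difference: with half the risk (k = 0.5), m is 0.90 at f = 0.20 and 0.75 at f = 0.50.

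**What the mixed model changes.** The patient random intercept lets residents seen in both periods contribute within-person information, which late recruits do not distort. Large simulated datasets (gamma frailty in place of the random intercept, no cluster effect, 5- and 7-month periods, rate 0.75, true ratio 1.00, k = 0.80, frailty variance 0.5 to 4) gave an estimated ratio of about 0.96-0.98 at f = 0.20 and 0.91-0.97 at f = 0.50. The bias shrinks but does not vanish. The crude figures are the outer end for these assumptions.

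**The case against.** The strongest reply is that selection is inferred, not documented. Eligibility criteria and recruitment has the organisations identify residents against listed criteria, hand over information and ask permission for an approach; a visiting researcher or nurse takes consent. A reader might infer that staff who received the UTI training choose whom to enrol. The article does not say so: it does not describe a choice among eligible residents, and it does not say that the identifiers are the trained staff. That inference should not be made. What stands is that identification lies with the randomised, unblinded organisation after allocation, which leaves the route for selection open. Not stating the aims to control clusters limits knowing selection there, but not in intervention clusters.

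Second, adjustment is already planned. The eight-factor model is prespecified, and patient characteristics are recorded at study entry, so late recruits should have them. This reduces the concern for measured factors. It does not settle it, because that model comes second and no model corrects for unmeasured selection.

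Third, timing. The timeline figure is not shown, and the article does not say when allocation occurred relative to baseline recruitment. That new residents enter after allocation is inferred from the pause falling inside the intervention period. The inference is sound, but it means that only the intervention start is a usable cut-off for a restricted analysis.

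Fourth, at the planned effect a 4-10% shift leaves the ratio near 0.48-0.59, which is unlikely to reverse the conclusion. That is fair. The shift would matter more if the true effect were small.

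**Conclusion.** The concern holds as a risk of bias, in either direction. The presumption of balance in the Discussion does not cover recruitment after allocation, and the first model cannot remove an arm-specific change in resident mix among recruits without baseline data. Under an assumed 20-50% share and a 20% risk shift in one arm, a crude null ratio would move to about 0.90-0.96 or 1.04-1.10, and less far under the mixed model. Both inputs are assumptions with no basis in the article, and a larger risk difference would give a larger shift.

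A reader might go further and infer that bias occurred, that it favours the intervention, or that late recruits make up a large part of follow-up. The article supports none of these. It reports deaths and a growing need for recruitment, without numbers, and gives no sign of the direction of any selection.

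**What to change.** By documented amendment before the database lock (planned for September 2021 under Trial status):

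1. Make the prespecified model with the eight resident factors the primary analysis, and report the unadjusted model beside it. Replace the statement that multiple imputation will be considered with a firm rule for missing covariates.
2. Add a prespecified sensitivity analysis restricted to residents included before the intervention start, with the same model.
3. In the Discussion, replace the presumption of balance with a comparison by arm of the number and entry characteristics of residents recruited after the intervention start.

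The factors and inclusion dates should already be on file, so no new data collection is needed. The costs are the amendment itself, which must be dated and justified because the trial is unblinded and under way; the decision on missing covariates; and a wider confidence interval in the restricted analysis. Adjustment addresses measured differences only, which is why the restricted analysis is needed as well.
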